### Ethical Considerations

This study was approved by the ethics committee of Union Hospital, Tongji Medical College, Huazhong University of Science and Technology (approval 2024-0833-02). Written informed consent will be obtained from all patients prior to the initiation of study procedures. Participants aged 18 to 75 years will receive a comprehensive explanation of the study’s background, objectives, methodology, potential benefits, risks, and any possible inconveniences. Their rights as research participants will also be clearly outlined. All questions will be addressed thoroughly by the research team to ensure full understanding before consent is given. Participation in this study is entirely voluntary. Consent forms must be signed by the participant, or in cases involving minors or individuals unable to provide consent, by a parent or legally authorized representative. A model informed consent form has been provided and uploaded in Multimedia Appendix 2. This study will be conducted in accordance with the approved protocol and the ethical principles set forth in the current version of the Declaration of Helsinki. All participants were provided with surgical accident insurance. The research team will cover all the treatment costs for study-related complications as assessed and approved by the ethics committee. The data collected in this study will be de-identified. The results will be submitted for publication in an international peer-reviewed journal with anonymized data.

### Statistical Methods

#### Hypothesis

##### Null Hypothesis

The rate of POPF in patients who undergo pancreatic stump ligation is not lesser than that using other closure techniques.

##### Alternative Hypothesis

The rate of POPF in patients who undergo pancreatic stump ligation is lesser than that using other closure techniques.

#### Sample Size Calculation

Based on published clinical studies on the incidence of pancreatic fistula [6-8] using other closure techniques, the incidence of POPF was set at 40%. On the basis of the results of previous animal experiments, the expected incidence of POPF in the ligation strategy is 5%. Using the formula *n = 2p̅q̅(Z_α_+Z_β_)^2^/(p1-p2)^2^* for sample size calculation with the probability of type I error of .05 and the statistical power of .90, we estimated that 30 participants should be included in each group.

#### Statistical Analysis

All statistical analyses will be conducted using SAS software (version 9.3; SAS Institute). Normality tests will be conducted for measurement data, describing the mean, standard deviation, median, quartiles, minimum, and maximum values based on the distribution type. Count data will describe the number and percentage of cases in each category. The rate effect indicator will reflect the effective rate and 95% CI. Missing values will not be filled in for research purposes and will not be included in the calculation of percentages unless otherwise specified. Stratified analyses will be conducted on the basis of pancreatic texture. A logistic regression analysis for POPF will be performed to identify its independent risk factors.

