**Methods:**

In this nonrandomized controlled clinical study at a tertiary center in China, the major eligibility criterion is the presence of lesions planned for distal pancreatectomy. Sixty patients will be allocated to the experimental or control group according to their choice. Recruitment for either group will be discontinued upon reaching the predefined sample size of 30 participants. In the experimental group, the pancreas will be ligated 5 mm from the pancreatic stump with a quantified force to provide a pancreatic duct burst pressure of approximately 40-70 mm Hg. The ligation force will be provided by a 3.2-mm-diameter silicone ring. During pancreatic stump ligation, this silicone ring will be stretched to 15 mm, generating an applied force of 1.3 N. The pancreas will be severed using energy-based devices before or after the ligation. In the control group, the pancreatic stump will be managed by manual suturing or stapling closure according to the surgeon’s clinical judgment and preference. Postoperative regular follow-up examinations will be conducted. The primary outcomes include postoperative pancreatic fistula and postoperative hospital stay, and the secondary outcomes include intra-abdominal infection, incision infection, and postoperative treatment costs. The primary and secondary outcomes of patients in this cohort will be statistically compared using appropriate tests.

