### Group Allocation

Patients will be allocated to the experimental or control group according to their choice. Recruitment for either group will be discontinued upon reaching the predefined sample size.

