Pancreatic texture and patient age are important factors influencing the occurrence of POPF. To align our study with real-world clinical scenarios, we will not restrict enrollment to patients with specific pancreatic texture characteristics. Instead, we will employ a stratified analysis based on pancreatic texture during data interpretation to mitigate the potential bias arising from variations in tissue consistency. Furthermore, to reduce the confounding effect of age on the risk of POPF, we will limit participant enrollment to individuals younger than 75 years [25,26].

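### Groups are formed by patient choice, but beyond texture strata with no pooled estimate and an upper age limit, no confounder-adjusted effect of ligation on POPF is stated

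*Protocol article*

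**What the plan says.** On allocation, the Group Allocation section states: "Patients will be allocated to the experimental or control group according to their choice". The Objective and the Hypothesis section put a causal, directional question: whether POPF is less frequent with ligation than with other closure techniques.

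The article describes the analysis in these places:

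- The abstract's Methods paragraph: "The primary and secondary outcomes of patients in this cohort will be statistically compared using appropriate tests".
- Statistical Analysis, on the effect measure: "The rate effect indicator will reflect the effective rate and 95% CI".
- Statistical Analysis, on texture: "Stratified analyses will be conducted on the basis of pancreatic texture". The Discussion (Overview) gives the purpose: "we will employ a stratified analysis based on pancreatic texture during data interpretation to mitigate the potential bias arising from variations in tissue consistency".
- Statistical Analysis, on regression: "A logistic regression analysis for POPF will be performed to identify its independent risk factors".
- Discussion (Overview), on age: "to reduce the confounding effect of age on the risk of POPF, we will limit participant enrollment to individuals younger than 75 years".

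The Limitations section names the nonrandomised design as a primary limitation. The biases it derives from that design and from the lack of blinding are performance bias and detection bias. Confounding is not named there.

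**The concern.** When patients choose their group, the groups may differ in factors that drive POPF, and a crude difference mixes those with the effect of ligation. The article itself calls texture and age important for POPF, yet it assigns an adjusted group effect to neither.

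- **Texture** is to be stratified, but no estimate or test is pooled over the strata, so the stratification does not produce one adjusted answer to the hypothesis.
- **Age** is handled by an upper enrolment limit. Eligibility from 18 to 75 still spans 75 − 18 = 57 years.
- **The regression** is described as a search for risk factors. The article does not say that group is in the model, or that the group coefficient is a result.
- **The effective rate** corresponds to none of the listed primary or secondary end points. A rate with its interval is also not a comparison of two groups.

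At stake is the trial's main claim. If the plan is followed as written, a difference in case mix could be reported as an effect of ligation, or could hide one.

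**Working it through.** **1. The plan's own figure.** Inputs from Sample Size Calculation: p1 = 0.40, p2 = 0.05, type I error .05, power .90, and n = 2·p̄·q̄·(Zα+Zβ)²/(p1−p2)². With p̄ = 0.225, q̄ = 0.775 and two-sided Zα: n = 2 × 0.225 × 0.775 × (1.960 + 1.282)² / 0.35² = 29.91, so 30 per group. The stated size reproduces. It is the size for a crude comparison of two proportions.

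**2. How far a crude test can mislead.** The inputs here are assumptions, not figures from the article. Ligation has no effect; POPF risk is 50% in soft and 20% in firmer glands (or 55% and 15%); the soft-gland share differs between groups. A group's crude rate is share × soft risk + (1 − share) × firmer risk. Example at 30% versus 70% soft: ligation 0.3 × 0.50 + 0.7 × 0.20 = 0.29; control 0.7 × 0.50 + 0.3 × 0.20 = 0.41.

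The chance of a false benefit is the exact binomial probability, at 30 per group, that z = (control rate − ligation rate)/√(p̄q̄·2/30), with p̄ the observed pooled rate, exceeds 1.96.

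| Soft glands, ligation vs control | Risks 50%/20%: crude rates | False benefit | Risks 55%/15%: crude rates | False benefit |
|---|---|---|---|---|
| 45% vs 55% | 33.5% vs 36.5% | 4.1% | 33% vs 37% | 4.9% |
| 40% vs 60% | 32% vs 38% | 6.7% | 31% vs 39% | 9.1% |
| 30% vs 70% | 29% vs 41% | 15.6% | 27% vs 43% | 24.7% |
| 70% vs 30% | 41% vs 29% | 0.2% | 43% vs 27% | 0.05% |

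With no imbalance the figure is about 2.4%. The last row shows the opposite direction: confounding then works against ligation.

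**3. The same null with a pooled stratified test.** The Mantel-Haenszel statistic sums observed minus expected events over strata and divides by the root of the summed hypergeometric variances. In 200,000 simulated trials with two strata, false benefit at 30/70 is about 2.6-2.8%, and at 40/60 about 2.5%.

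**4. Power of the pooled test at the planned effect.** Power is about 0.94-0.95 with balanced texture, with two or three strata. At 30/70 it was about 0.77-0.89, depending on the assumed stratum risks. One example: control risks 50% and 30%, and ligation risks one eighth of these (5/40), give 0.94 balanced and 0.89 at 30/70.

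**5. What the data can support.**

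- Expected POPF events at the design rates: 30 × 0.40 + 30 × 0.05 = 13.5.
- Group, three-level texture and linear age use 1 + 2 + 1 = 4 parameters: 13.5/4 = 3.4 events per parameter.
- The chance of no event in the ligation arm is 0.95³⁰ = 21%; ordinary logistic regression then has no finite group estimate.
- If texture splits evenly over three grades, each stratum has about 10 patients per arm and 4 versus 0.5 expected events. Separate stratum results cannot carry the conclusion.

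**The case against.** The strongest reply has four parts.

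*The plan does address confounding.* It stratifies by texture, says this is to limit bias, and restricts age with the declared aim "to reduce the confounding effect of age on the risk of POPF". This stands. A reader might infer that the plan offers nothing beyond a crude comparison and a risk-factor search; the text does not support that. What is missing is a step that turns these measures into one adjusted group effect.

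*The illustration uses the one factor that the plan stratifies on, and an extreme imbalance.* This also stands in part. Texture is graded during surgery, so patients cannot choose on the grade itself, only on preoperative correlates. If choice were unrelated to texture and half the glands were soft, a gap of at least 12 of 30 in that direction would arise with probability of about 0.13%. The 40/60 row is the fairer guide. The figures show what happens if the crude test is the headline; they do not predict the bias in this trial.

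*A regression for independent risk factors is usually multivariable and could include group, and a condensed article may leave covariates to the SAP.* A missing covariate list would indeed be no finding. But the article does state what the regression is for, and that purpose is not the ligation effect. It also names an effect measure that fits no end point.

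*The spurious differences are smaller than the planned effect.* True: 6-16 points at 40/60 and 30/70, against 35 planned. But significance does not require an observed difference of 35 points, as the false-benefit rates show.

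**Conclusion.** The point holds in a limited form. With allocation by choice, the article specifies no confounder-adjusted effect of ligation on POPF beyond unpooled texture strata and an age limit. The headline difference may be confounded.

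Two stronger readings go too far: that the result will be confounded, and that the bias will favour ligation. Neither the direction nor the size of any imbalance is known from the article. An imbalance the other way would work against ligation.

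If texture is imbalanced and the crude test is the headline, false benefit is about 7-9% at 40/60 and 16-25% at 30/70, instead of about 2.4%. These figures rest on the assumed texture risks and shares, on a single binary factor, and on 30 patients per group. Age and other case-mix differences are not quantified here. The gap matters because the primary causal claim depends on it, and the data needed to close it are texture, which is already graded, and age, which eligibility requires.

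**What to change.** Before outcome data are analysed, reword the analysis as follows.

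1. **Primary POPF analysis:** the Mantel-Haenszel risk difference (ligation minus control) with 95% CI and test, pooled over the recorded texture strata.
2. **Supporting analysis:** one prespecified model with group, texture and continuous age all forced in, by a penalised (Firth) or overlap-weighted method. The expected 13.5 events, and the 21% chance of none in the ligation arm, rule out reliance on ordinary logistic regression or a long covariate list.
3. **Secondary:** the crude difference with its interval, for comparison.
4. **Effect measure:** replace the effective rate with the between-group POPF risk difference.
5. **Reporting:** name confounding in the Limitations, and base the conclusion on the adjusted estimate.

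The risk-factor regression can stay as an exploratory analysis. Recruitment, treatment and data collection are unchanged. The cost to disclose is power: about 0.94-0.95 if texture is balanced, but possibly about 0.77-0.89 under a 30/70 imbalance. Adjustment for texture and age also leaves unmeasured confounding in place, so the result remains that of a nonrandomised comparison.

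### At the planned rates the POPF logistic regression has about 13 to 14 events: too few to identify several independent risk factors reliably, with a 21% chance that the group odds ratio is not finite

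*Protocol article*

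**What the plan says.** The Statistical Analysis section of the protocol article states two analyses of POPF beyond the descriptive summaries. One is by texture: "Stratified analyses will be conducted on the basis of pancreatic texture". The other is the regression: "A logistic regression analysis for POPF will be performed to identify its independent risk factors". The second fixes a purpose. Several factors are to be identified, each adjusted for the others. It does not fix covariates, their number or the estimation method.

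The information available follows from Sample Size Calculation. For other closure techniques "the incidence of POPF was set at 40" per cent, and from animal experiments "the expected incidence of POPF in the ligation strategy is 5" per cent. The calculation is run "with the probability of type I error of .05 and the statistical power of .90". Its result is given in these words: "we estimated that 30 participants should be included in each group".

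Two other statements bear on the model. The Discussion overview says "Pancreatic texture and patient age are important factors influencing the occurrence of POPF", and texture is graded at three levels during the operation. Group Allocation says "Patients will be allocated to the experimental or control group according to their choice", so the groups may differ in factors that influence POPF.

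**The concern.** A search for independent risk factors draws its information from the number of events, and this trial is designed to have few. If ligation performs as planned, nearly all events fall in the control group and the ligation group contributes one or two, or none.

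Two things can go wrong. With several terms, coefficients are imprecise and overfitted, so the factors reported depend heavily on chance. If no ligated patient has POPF, the ordinary maximum-likelihood odds ratio for group runs off to its limit and the Wald p-value becomes uninformative. That is most likely when ligation works best. Because patients choose their group, readers will look to this regression for reassurance on confounding: it is the only multivariable analysis stated.

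**Working it through.** **1. The plan's own figure.** The stated formula uses p1 = 0.40, p2 = 0.05, mean p = 0.225 and q = 0.775. With two-sided alpha 0.05 and power 0.90, n = 2 × 0.225 × 0.775 × (1.960 + 1.282)² / 0.35² = 29.9, so 30 per group. The plan's figure is reproduced. (One-sided alpha gives 24.4, so 25.)

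**2. Events available.** Expected events are 30 × 0.40 + 30 × 0.05 = 12 + 1.5 = 13.5. Convolving the two binomial distributions exactly gives a median of 13 and a 5th to 95th percentile of 9 to 18. The chance of 20 or more events is 2.3%.

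**3. Events per parameter.** An illustrative model is built from the factors the article names: group (1), texture at three levels (2) and age (1), so 4 parameters. 13.5 / 4 = 3.4.

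**4. Sensitivity to the ligation rate** (control rate held at 40%; the chance of no ligation event is (1 − rate)^30):

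| Ligation rate | P(no ligation event) | Expected events | Events per parameter (4) |
|---|---|---|---|
| 2% | 55% | 12.6 | 3.2 |
| 5% (plan) | 21% | 13.5 | 3.4 |
| 10% | 4% | 15.0 | 3.8 |
| 20% | 0.1% | 18.0 | 4.5 |

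The separation risk depends strongly on the ligation rate. The shortage of events does not.

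**5. What one favourable factor would need.** Assume a binary factor that splits each group evenly and is unrelated to the other terms. The information on its log odds ratio near the null is the sum over groups of n × p × (1 − p) × 0.25. This is 30 × 0.40 × 0.60 × 0.25 = 1.80 for control and 30 × 0.05 × 0.95 × 0.25 = 0.36 for ligation, in total 2.16. The standard error is 1/√2.16 = 0.68, and exp(1.96 × 0.68) is about 3.8. So an observed odds ratio of about 3.8 only just reaches the 5% level. At a 20% ligation rate the total is 1.80 + 1.20 = 3.00 and the threshold is exp(1.96/√3.00), about 3.1. Uneven or correlated factors need more. This is a large-sample approximation.

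**6. Simulation at 40% versus 5%.** Assumptions: texture shares of 50/30/20% and covariates with no true effect. Shrinkage is (LR − df)/LR among finite fits.
- Group only: finite in 79% of datasets, median shrinkage 0.91.
- Group, texture and age: no finite fit in about 26%, median shrinkage 0.71.
- Eight parameters (1.7 events each): median shrinkage 0.57, and 26% of finite fits flag at least one false factor. That last figure mainly reflects testing seven null terms (1 − 0.95^7 = 30%). It shows the hazard of an open search and not an inflated error rate per term.

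**The case against.** The strongest reply is that the article need not specify this model. Covariates, selection rules and estimation method are commonly left to an SAP, which is not shown here and could limit the terms or penalise the fit. That stands: the missing covariate list is not a finding, and the four-parameter model is only an illustration. The stated purpose is a different matter. Penalisation makes estimates finite but adds no events, so a well-written SAP would still have to give up or demote that aim.

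A reader might infer that the regression is bound to fail or cannot be estimated. The figures do not support this. At the plan's rates there is at least one ligation event in about 79% of trials, and the four-parameter model was finite in about 74% of simulated datasets. The 21% also rests on a 5% rate drawn from animal experiments.

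A reader might also infer that the trial's main conclusion is at risk. It is not. The hypotheses and the sample size concern a comparison of two POPF rates, and that comparison remains possible with no ligation events. The regression is given a risk-factor purpose and is not named as the adjusted treatment estimate.

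Nor can the texture analysis be faulted for underpowered tests within strata. The article presents stratification as a way to reduce bias, does not say that each stratum will be tested, and gives no texture distribution from which stratum sizes could be worked out.

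Finally, the Limitations section concedes a small sample and leaves room to enlarge it. It does not link this to the regression, and it gives no enlarged size that could be credited.

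**Conclusion.** The concern holds for a secondary analysis. With about 13 to 14 expected events, or 15 to 18 if the ligation rate is 10% to 20%, the planned regression cannot reliably identify several independent risk factors. If the 5% rate is true, there is also a 21% chance that the maximum-likelihood odds ratio for group is not finite. That chance is larger if ligation does better than planned and becomes negligible by a 20% rate.

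The event counts and zero-event probabilities rest only on 30 patients per group, a 40% control rate and the ligation rates shown. The 3.4 events per parameter rests on the illustrative model, and the simulation figures on assumed texture shares and null covariates. The conclusion about risk factors does not depend on the 5% rate being right. The change should be made before the data are analysed.

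**What to change.** - Fit a Firth-penalised logistic regression with profile-penalised-likelihood 95% confidence intervals. Restrict it to a small prespecified set: group forced in, texture and age.
- Describe it as a supportive adjusted estimate of the group effect. Withdraw the claim to identify independent risk factors, and show other factors descriptively or label them exploratory.
- If the texture strata are summarised across groups, pool them with a Mantel-Haenszel stratified risk difference. A Mantel-Haenszel odds ratio would not serve: with no ligation events it is zero and has no finite interval on the log scale.

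The set must stay small because penalisation does not remove the shortage. Even three parameters, for example with texture reduced to two levels, would have 13.5 / 3 = 4.5 events each.

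The cost is a change of wording and one software option, with no new patients or data. The exploratory risk-factor claim is given up and the estimates are slightly shrunk. The primary comparison of POPF rates is unchanged.

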## Results

The version number and date of the protocol are version 2.0 and January 22, 2025, respectively. Participant recruitment for this study commenced in February 2025 and will conclude when the estimated sample size is achieved (in or around September 2025); thereafter, the follow-up assessments will be completed (in or around December 2025). No specific funding was received for this study.

## Discussion

### Overview

POPF after distal pancreatectomy remains an unresolved issue [13,22]. The existing stump-closure techniques primarily include manual suturing and stapling, both of which carry a high risk of POPF. Animal studies suggest that the balance between pancreatic duct burst pressure and pancreatic tissue necrosis may be a key factor influencing the occurrence of POPF after distal pancreatectomy. We attempted to address this issue by ligating the pancreatic stump with an appropriate quantified amount of force.

Although suturing MPD has been shown to reduce the risk of POPF [23,24], MPD is difficult to ligate due to its location within the pancreatic parenchyma, and MPD is often difficult to locate during surgery. Therefore, the method adopted in this study involves ligating the pancreatic stump rather than MPD. Through experiments on specimens from patients with pancreatic space-occupying lesions, we found that for pancreas with soft, medium, and hard textures, ligation forces of 2.5 N using 4 strands of size-0 braided nonabsorbable silk suture or 1.3 N using 2 strands of size-0 braided nonabsorbable silk suture were sufficient to achieve a pancreatic duct burst pressure of 40-70 mm Hg. Therefore, we initiated a prospective clinical study on this pancreatic stump treatment technique, which yielded the optimal pancreatic duct burst pressure by quantifying the ligation force. The aim of this study was to determine whether this technique can reduce the risk of POPF and provide new insights into pancreatic stump closure.

Theoretically, potential surgery-related adverse events for participants of the new approach may primarily include pancreatic fistula, hemorrhage, and pancreatitis. All adverse events occurring during both the intervention and follow-up periods will be documented and submitted to the ethics committee regularly. Should the predefined criteria be met, immediate actions will include either termination of an individual participant’s trial eligibility or discontinuation of the entire study.

Pancreatic texture and patient age are important factors influencing the occurrence of POPF. To align our study with real-world clinical scenarios, we will not restrict enrollment to patients with specific pancreatic texture characteristics. Instead, we will employ a stratified analysis based on pancreatic texture during data interpretation to mitigate the potential bias arising from variations in tissue consistency. Furthermore, to reduce the confounding effect of age on the risk of POPF, we will limit participant enrollment to individuals younger than 75 years [25,26].

